#### Secondary outcomes

##### Nepean dyspepsia index - Korean version

The Nepean dyspepsia index (NDI), a disease-specific instrument used to assess GERD symptoms [31], is a reliable and valid questionnaire [32, 33]. In this trial, the Korean version of NDI (NDI-K) will be used. It was validated in 2004 by Lee et al. [34] and contains 40 items comprising two sections: symptom-based questions (duration, severity, and degree of 15 separate symptoms), and those pertaining to the quality of life (QoL). The patient will complete the questionnaire at baseline, visit 6, and visit 12.

##### Gastrointestinal hormone (gastrin, motilin)

GERD is related to weakness in the lower esophageal sphincter [35], and motilin [36] and gastrin [37, 38] have been reported to increase strength of the lower ESP (LESP). Motilin is an endogenous gastrointestinal hormone that increases upper GI tract motility, and it is considered an endogenous prokinetic hormone [39]. Gastrin is also a gastrointestinal polypeptide; it is thought to stimulate the lower esophageal sphincter by increasing the LESP [40]. However, controversy exists regarding whether EA increases gastrin and motilin levels [11, 13–16], so we will attempt to confirm the influence of EA on increases in motilin and gastrin in this trial. Specifically, a nurse will collect a 10-mL blood sample, in which the serum will be separated using a centrifuge. The sample will be analyzed using both a Human Motilin ELISA kit and a Human Gastrin ELISA kit (Mybiosource Inc., San Diego, California, USA). This will be carried out at baseline and visit 12.

##### Inflammatory cytokines

One report has claimed that cellular inflammatory processes are involved in the pathogenesis of GERD and its complications [17]. On this basis, we will evaluate serum IL-1, IL-6, IL-8, IL-4, and IL-10 (all inflammatory mediators) using the BD Facscalibur™ (BD Bioscience, CA, USA) at baseline and visit 12. IL-8 is expressed at high levels in the affected mucosae of patients with GERD [41–43]. IL-1, IL-6, IL-10, and IL-4 are also important mediators of the inflammatory responses related to GERD [17]. Through this analysis, we will clarify the influence of EA on the levels of cytokines, as well as the relation between these results and subjective symptoms.

##### EuroQol-5 Dimension

The EuroQol-5 Dimension (EQ-5D) [44] will be used to evaluate the participants’ QoL. The EQ-5D is a standardized preference-based questionnaire for measuring health-related QoL [30]; it consists of the EQ-5D index and the EQ-5D visual analog scale (VAS). The EQ-5D index is calculated on the basis of five dimensions: mobility, self-care, ability to undertake usual activities, pain, and anxiety/depression. The EQ-5D VAS measures the participant’s current health status using a standard vertical 20 cm VAS [45]. The top of this line is labeled “best imaginable health state” and the bottom “worst imaginable health state.” We will use a validated Korean version of EQ-5D [46] at baseline, visit 6, and visit 12.

##### Korean gastrointestinal symptom rating scale

The Korean gastrointestinal symptom rating scale (KGSRS) [47] will be used to evaluate the gastrointestinal discomfort of participants. This questionnaire consists of 16 items covering both upper and lower gastrointestinal symptoms. In this trial, we will evaluate changes in reflux, abdominal pain, and indigestion after treatment. The evaluation will be carried out at baseline, visit 6, and visit 12.

##### Eleven-point numerical rating scale

Participants will be asked to check the discomfort caused to them by GERD using an 11-point numerical rating scale. This will be performed at baseline, visit 6, and visit 12.

##### Perceived stress scale

The perceived stress scale (PSS) was developed and validated by Cohen et al. in 1983 [48]. We will use the PSS translated into Korean and validated by Lee [49]. This questionnaire evaluates a participant’s perceived stress during the last 1 month using a 5-point scale.

##### Blinding index and credibility assessment

Blinding of participants will be assessed using a blinding index (BI) [50]. Participants will answer the following question for each acupuncture point: “What type of acupuncture do you think you received?” The answer will be selected from three choices: “classic electroacupuncture,” “non-classic electroacupuncture,” or “don’t know.” In addition, the credibility of the treatment will be evaluated using the credibility assessment questionnaire. These evaluations will be conducted after EA treatment at visit 12.

##### Pattern identification for gastroesophageal reflux disease

The participants’ pattern will be classified using pattern identification for gastroesophageal reflux disease (PIGERD) [21]. Participants will be assigned EA treatment on the basis of the result of the PIGERD. This identification will be performed at visit 1 and visit 12.

##### The acupuncture beliefs scale

We will assess the participant’s belief in the efficacy of EA at visit 1 using the acupuncture beliefs scale [51], which consists of 36 items. Participants will respond on a 5-point Likert scale as follows: “strongly agree” (1 point), “agree” (2 points), “neutral” (3 points), “disagree” (4 points), and “strongly disagree” (5 points).

##### Patient global impression of change

The EA will be globally assessed by the participants using patient global impression of change—a self-reported seven-point categorical scale that is used to evaluate overall improvement after EA treatment [52]. Participants will evaluate improvements in their symptoms between baseline and visit 6, as well as between baseline and visit 12, by choosing one of the following answers: (1) very much improved, (2) much improved, (3) minimally improved, (4) no change, (5) minimally worse, (6) much worse, or (7) very much worse.

##### Qi-stagnation questionnaire

In traditional Korean medicine, the concept of qi stagnation is similar to that of stress in Western thinking [53]. The qi stagnation questionnaire is composed of 11 subjective items and one objective item; the items are used to diagnose qi stagnation. Using this questionnaire, we will evaluate the degree of qi stagnation in patients with GERD at visit 1 and visit 12.

##### Spleen qi deficiency questionnaire

The spleen qi deficiency questionnaire [54] will be used to diagnose whether the participant is in a state of spleen qi deficiency. This questionnaire consists of nine items concerning symptoms and two items regarding tongue and pulse diagnosis. The diagnosis will be performed at visit 1 and visit 12 by a KMD.

##### Evaluation of rescue medicine

We will quantify the amount of rescue medicines taken between visits.

### Sample size calculation

The required sample size was calculated on the basis of the difference in PR between the EA and sham EA groups. On the basis of previous research [55], we assumed the PR would be 92.8 % in the treatment group and 57.1 % in the control group. With a 5 % false positive error (*α* = 0.05, two-sided) and 80 % power (*ß* = 0.2) the required sample size in each group was *n* = 21.9. Assuming a 25 % of dropout rate, the real-world sample size will be *n* = 30 in each group, for a total of 60 participants.

### Statistical analysis

An independent statistician blinded to group allocation will carry out the statistical analysis using SPSS™ 18.0 (SPSS Inc., Chicago, Illinois, USA). All final data will be securely stored, and only the statistician will have access. We will perform both intention-to-treat (ITT) and per protocol (PP) analysis, with all analyses being based on the ITT principle. Any participant who receives EA more than nine times during the study period will be eligible for PP analysis.

For ITT analysis of secondary outcomes, we will use the “last observation carried forward” rule. In the case of the primary outcome, however, missing values will not be replaced, because of the characteristics of adequate relief (AR). We will only count actual responses regarding AR. When AR occurs in more than 50 % of the treatment sessions in which a study subject participated, the participant will be classified as a responder. All data will be shown as the mean ± standard deviation (SD) or as numbers and percentages. The statistical significance level will be set at 0.05 (two-sided), with 95 % confidence intervals (CI). The analysis for safety will also follow the principles of ITT.

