### Withdrawal criteria

Participants will be withdrawn from the study if they (1) miss a scheduled EA treatment three times in a row or (2) take forbidden medication, herbal medicine, or undergo surgery related to GERD during the study period.

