#### Secondary outcomes

The independent t test will be used to evaluate changes in the NDI-K score after 6 weeks of treatment. If there is a covariate at baseline, an ANCOVA will be performed. To compare variables between the two groups, the two-sample t test will be used for parametric analyses, and the Mann-Whitney U test, for nonparametric analyses.

A repeated measures analysis of variance or repeated measured ANCOVA will be used to analyze group-by-time interactions, as well as intergroup differences. The *χ*^2^ test or Fisher’s exact test will be used to analyze nominal variables in each group as well as to compare AEs between groups.

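### Last observation carried forward for all secondary outcomes sets every dropout's change to zero on the measures taken only at baseline and end, and shrinks or distorts the estimated effects

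*Protocol article*

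**What the plan says.** The Statistical analysis section fixes the rule for every secondary outcome: "For ITT analysis of secondary outcomes, we will use the “last observation carried forward” rule". The primary outcome is treated differently: "In the case of the primary outcome, however, missing values will not be replaced". The only other analysis set is per protocol, for participants with more than nine sessions.

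Table 2 and the outcome sections give two schedules:

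- **Baseline and end only:** gastrin and motilin ("This will be carried out at baseline and visit 12"), the cytokines, and the qi-stagnation and spleen-qi-deficiency questionnaires.
- **Baseline, V6 and end:** NDI-K, the numerical rating scale, KGSRS, EQ-5D and PSS. PGIC is taken at V6 and the end and has no baseline value.

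The text calls the last assessment visit 12 and Table 2 places it at V13. That does not affect this point.

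For analysis, the Secondary outcomes part of the statistical section uses t tests on change, and adds: "A repeated measures analysis of variance or repeated measured ANCOVA will be used to analyze group-by-time interactions".

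Under Withdrawal criteria: "Participants will be withdrawn from the study if they (1) miss a scheduled EA treatment three times in a row", or if they "take forbidden medication, herbal medicine, or undergo surgery related to GERD during the study period". The sample size section allows for losses: "Assuming a 25 % of dropout rate".

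**The concern.** Carrying a value forward assumes that a participant who leaves would have stayed at the last recorded value until week 6. On a measure with no intermediate visit, that value is the baseline, so the plan assumes no change at all in anyone lost, in either arm. On the three-visit scales the assumption is milder but still arbitrary: early losses get zero change, and later losses have a mid-treatment value analysed as a week-6 value. For PGIC, nothing exists to carry before V6.

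The trial sets out to clarify what electroacupuncture does to gastrin, motilin and cytokines, and how these relate to symptoms. Those conclusions rest on the measures where the rule does most damage.

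The withdrawal rule bears on the same question. Participants enter still symptomatic after standard treatment, and taking a forbidden GERD drug is a ground for withdrawal. Loss is therefore plausibly related to outcome, and the analysis is still described as intention-to-treat.

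**Working it through.** **1. The plan's own figure.** Inputs from the sample size section: 92.8% and 57.1% responders, two-sided 0.05, 80% power, 25% dropout. With a pooled variance, mean proportion (0.928 + 0.571)/2 = 0.7495:

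n = [1.96·√(2·0.7495·0.2505) + 0.8416·√(0.928·0.072 + 0.571·0.429)]² / 0.357² = 21.9

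Rounded up this is 22, and 22/0.75 = 29.3, so 30 per arm. The stated size reproduces. It concerns the primary outcome and does not depend on the carry-forward rule. The dropout allowance means 0.25 × 30 = 7.5 participants per arm.

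**2. Attenuation on end-only measures.** Let a fraction d of each arm drop out at random, with true mean changes m_E and m_S. Dropouts are assigned zero, so the estimated difference is (1 − d)(m_E − m_S). With d = 0.25 the factor is 0.75, and 0.5 SD becomes 0.375 SD.

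**3. Unequal dropout, no true effect.** Both arms change by m. On an end-only measure the spurious difference is m(d_S − d_E). Assuming m = 1 SD and dropout of 15% (EA) against 35% (sham), it is 1 × (0.35 − 0.15) = 0.20 SD. On a three-visit scale, assume half the dropouts leave before V6 and half the change is reached by V6. A dropout is then credited on average with 0.5 × 0 + 0.5 × 0.5m = 0.25m, so the difference is 0.75 × 0.20 = 0.15 SD. Swapping the dropout rates reverses the sign.

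**4. Interval width, end-only measure.** With a change SD of 1 and 25% zeros, the variance in an arm with mean change m is 0.75 + 0.1875m². The half-width ratio against 22.5 observed per arm is √[(v_E + v_S)/30] / √(2/22.5):

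| Mean change, EA / sham (SD, assumed) | Ratio | Narrower by |
|---|---|---|
| near 0 / near 0 | 0.2236/0.2981 = 0.75 | 25% |
| 0.5 / 0.5 | 0.2305/0.2981 = 0.77 | 23% |
| 1.2 / 0.5 | 0.2461/0.2981 = 0.825 | 17–18% |

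**5. Simulation.** 30 per arm and 6,000 runs per scenario. Assumptions not in the documents: SD 1 at each visit, correlation 0.5, half the change reached by V6, half the dropouts before V6, random dropout.

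| Scenario | Measure | Estimate (SD) | SE, carried forward | SE, observed data | Coverage of nominal 95% interval |
|---|---|---|---|---|---|
| Effect 0.70, sham change 0.5, 25% each | three-visit | 0.565 | 0.254 | 0.297 | 91.5% |
| same | end-only | 0.523 | 0.245 | 0.298 | 88.7% |
| No effect, change 1, EA 15% / sham 35% | three-visit | +0.142 | 0.256 | 0.301 | 91.7% |
| same | end-only | +0.203 | 0.247 | 0.300 | 87.0% |
| No effect, change 1, EA 35% / sham 15% | three-visit | −0.146 | 0.256 | 0.301 | 91.4% |
| same | end-only | −0.199 | 0.248 | 0.302 | 87.7% |
| No effect, change 1, 25% each | three-visit | −0.002 | 0.257 | 0.298 | 94.7% |
| same | end-only | −0.005 | 0.249 | 0.298 | 95.0% |

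The estimates agree with steps 2 and 3 (0.75 × 0.70 = 0.525; 0.8125 × 0.70 = 0.569). Intervals are about 14% narrower (0.257/0.298) to 18% narrower (0.245/0.298).

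**The case against.** Several stronger conclusions are tempting, and the documents do not support them.

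- *The standard errors are wrong.* A reader might infer this from the narrow intervals. For the carried-forward estimator itself the standard error is about right: in the simulation it matched the estimator's actual spread (0.245 against 0.244 on the end-only measure). Coverage is lost mainly through bias. What stands is that the intervals imply more information than was observed and centre on a biased value.
- *The rule manufactures false positives.* With equal dropout and no effect there is no bias and coverage is 95%. With equal dropout and a real effect, the error is attenuation, and the test statistic falls only a little: 0.75/0.77, about 3%, or 0.75/0.825, about 9%. False effects under random loss need unequal dropout. The article does not predict that: its 25% is a sample-size allowance, not a forecast by arm.
- *Baseline becomes the week-6 result for every dropout.* This holds only for the end-only measures.
- *Outcomes are not collected after withdrawal.* The article says participants leave the study and describes no later assessment, but it does not rule one out. An article may leave a final assessment to the full protocol.
- *The main result is compromised.* The primary outcome is explicitly not imputed.

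The per-protocol analysis relies less on carried values. It is no remedy, because it selects participants on attendance after randomisation.

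**Conclusion.** The point holds for the secondary outcomes. The carry-forward rule is an explicit choice, not a detail left open, and on this visit schedule it builds in a zero change for every dropout on the hormones, cytokines and qi questionnaires.

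The 25% shrinkage on end-only measures follows from the plan's own dropout allowance, given equal and random loss. The possible bias of about 0.14 to 0.20 SD in either direction rests on assumed dropout of 15% against 35% and an assumed 1 SD change in both arms. The 14% to 25% narrowing depends on the assumed mean changes and the visit schedule, with the upper end needing mean changes near zero.

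This should be changed before analysis. It does not threaten the primary comparison.

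**What to change.** Replace the carry-forward sentence as follows.

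- **Outcomes with V6 and end values:** a likelihood-based repeated-measures mixed model with group, visit, group-by-visit and baseline, using all observed values. It should also replace the repeated-measures ANOVA, which in its usual form needs complete records. PGIC has no baseline value and should be analysed from its observed V6 and end values.
- **End-only measures:** baseline-adjusted ANCOVA on observed values, with multiple imputation as a sensitivity analysis.

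These methods assume that loss is explained by the data observed, so collecting the outcomes matters more than modelling them. The Withdrawal criteria and the intention-to-treat statement need to be reconciled: state that scheduled V6 and final assessments continue, with consent, for participants who meet a withdrawal criterion, and analyse them as randomised. This concerns data collection only and leaves the criteria and treatment rules untouched.

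The cost is revised analysis wording, a little more analysis work and some additional questionnaire contacts.

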	6b) Precise description of the control or comparator. If sham acupuncture or any other type of acupuncture-like control is used, provide details as for Items 1 to 3 above. - Participants in the sham EA group will receive acupuncture treatment after randomization twice weekly for 6 weeks. - Sham EA group: nonpenetrating, nonacupoint, nonelectric current (1) Device: Park sham device with sham needle (2) Acupoint: Eighteen acupoints. Each acupoint is 2 cm apart from the acupoints of EA group to the medial side. (The optional points in accordance with pattern identification will not be included) (3) Duration of treatment sessions: 20 minutes

*STRICTA* STandards for Reporting Interventions in Clinical Trials of Acupuncture; *EA* elctroacupuncture, *GERD*, gastroesophageal reflux disease, *ST* stomach, *PC* pericardium, *LI* large intestine, *LR* liver, *SP* spleen, *GB* gallbladder, *CV* conception vessel

The treatment will consist of 12 sessions across 6 weeks (two sessions each week); it will be performed by KMDs with more than 5 years of clinical experience in acupuncture, who will go through training and simulation to ensure identical acupuncture treatment in accordance with the SOPs. The minimum interval between treatment sessions will be 2 days. Lifestyle will be modified in both groups.

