#### Primary outcome

We set the “proportion of responders” (PR) [28, 29] as the primary outcome. PR is the proportion of participants who respond “yes” to more than half of the AR-related questions during the treatment period [30]. An assessor will ask the participants the following question at each visit during the treatment period (twice a week for 6 weeks): “Have you had adequate relief of the pain or discomfort caused to you by GERD since the last visit?” We will define AR as ‘improvement of GERD symptoms by ≥ 20 % since the last visit.

If participants report AR at more than half of all treatment sessions, they will be defined as responders, and we will compare the proportion of responders between the EA and sham EA groups.

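### The primary responder endpoint has two conflicting denominators: all 12 sessions in one section, only the sessions attended in another

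*Protocol article*

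**What the plan says.** The Primary outcome paragraph under Outcome measurement gives the definition in two ways. It first asks for a yes to "more than half of the AR-related questions during the treatment period". It then states: "If participants report AR at more than half of all treatment sessions, they will be defined as responders". The Intervention section plans 12 sessions, and Table 2 schedules the AR question at 12 visits (V2 to V13).

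The Statistical analysis section handles missing data for this endpoint differently: "missing values will not be replaced, because of the characteristics of adequate relief (AR). We will only count actual responses regarding AR". Its responder rule requires AR in over 50% of the "treatment sessions in which a study subject participated, the participant will be classified as a responder". The same section describes the work as "with all analyses being based on the ITT principle".

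Two other sections bear on the point. Withdrawal criteria remove participants who miss three consecutive sessions, or who "take forbidden medication, herbal medicine, or undergo surgery related to GERD during the study period". Distribution of rescue medicine overrides the participant's answer and records no relief when more than three rescue doses were taken between visits. No section says how a withdrawn participant is classified for the primary outcome.

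**The concern.** A responder count is a numerator over a denominator, and the article gives two denominators. Anyone who misses a session can be a responder under one and a non-responder under the other, so the same data can yield two different primary results. If the choice is left until the data are seen, it can be made with the result in view.

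The attended-sessions rule also fixes the ITT endpoint badly. It has no minimum number of sessions and no provision for withdrawal. A participant with relief at 2 of 3 sessions who is then withdrawn for taking a forbidden GERD drug is a responder (2/3), but under the all-sessions rule is not (2/12). This sits oddly beside the rescue-medicine override, under which heavy rescue use cancels a yes while withdrawal for a forbidden drug leaves responder status untouched. A randomised participant with no AR answer has the undefined status 0/0.

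**Working it through.** **The plan's own figure.** Inputs from Sample size calculation: 92.8% and 57.1% responders, two-sided 5% level, 80% power, 25% dropout. With the mean proportion 0.7495 and the pooled-variance formula:

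n = [1.960·√(2·0.7495·0.2505) + 0.8416·√(0.928·0.072 + 0.571·0.429)]² / 0.357² = (1.201 + 0.470)² / 0.1274 = 21.9

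Rounded up to 22, then 22/0.75 = 29.3, so 30 per arm. The figure reproduces. The inflation treats dropouts as not evaluable, which is what neither responder rule does.

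**Answers needed under each rule.** All-sessions: at least 7 of 12, whatever the attendance. Attended-sessions, by number attended:

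| Attended | 1 | 2 | 3 | 4 | 5 | 6 | 7 | 8 | 9 | 10 | 11 | 12 |
|---|---|---|---|---|---|---|---|---|---|---|---|---|
| Yes answers needed | 1 | 2 | 2 | 3 | 3 | 4 | 4 | 5 | 5 | 6 | 6 | 7 |

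Someone attending six or fewer sessions cannot be a responder under the all-sessions rule but can be under the other. The thresholds coincide only at 12.

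**Short attendance makes qualifying by chance easier in some cases.** With an assumed per-visit yes probability of 0.4, the attended-sessions rule gives a 35% chance of being a responder after 3 sessions and 16% after 12.

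**Effect on the planned comparison.** Assumptions, none of them in the document except the responder rates and the 25%: visits are independent; completers respond at the planned rates; dropouts have the completers' per-visit probability; the number of sessions a dropout attends is spread evenly over the range shown. Solving P(Bin(12, q) ≥ 7) = 0.928 and 0.571 gives q = 0.733 and 0.566. Each arm's responder rate is 0.75 × planned rate + 0.25 × average rate among dropouts. Power is by exact enumeration of the uncorrected χ² test with 30 per arm.

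| Sessions attended by dropouts | Attended-sessions rule: EA vs sham, difference, power | All-sessions rule: EA vs sham, difference, power |
|---|---|---|
| 1–6 | 88.3% vs 55.3%, 33.0 points, 84% | 69.6% vs 42.8%, 26.8 points, 56% |
| 1–11 | 90.2% vs 56.5%, 33.7 points, 87% | 75.5% vs 45.1%, 30.4 points, 68% |
| 7–11 | 92.4% vs 58.0%, 34.5 points, 91% | 82.5% vs 47.8%, 34.7 points, 82% |

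**If dropouts are mostly failures.** Give dropouts in both arms a per-visit probability of 0.2, leaving after 1–6 sessions. About 7% of them become responders under the attended-sessions rule. The rates are 0.696 + 0.25 × 0.074 = 71.5% and 0.428 + 0.25 × 0.074 = 44.7%, a difference of 26.8 points, the same as under the all-sessions rule.

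**Unequal dropout (1–6 sessions, dropouts like completers).** With 35% EA and 15% sham dropout, the difference is 30.5 points (attended) against 11.8 (all). Reversed, it is 35.5 against 41.8.

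**The case against.** The best defence is that the Statistical analysis section is the later, more specific text and the only missing-data rule for this endpoint. It is explicit ("We will only count actual responses regarding AR"), and the reference to AR-related questions can be read as questions actually put to the participant. A statistician would probably follow it. That narrows the dispute, but the sentence about all treatment sessions remains in the definition, and the attended-sessions rule would still lack any provision for withdrawn participants. The per-protocol analysis, limited to those treated more than nine times, would show how far the result depends on early leavers; it does not repair the ITT rule. The rescue override limits misclassification after heavy rescue use but does not cover forbidden drugs or loss to follow-up. Handling of the 0/0 participant may be settled in an analysis plan that is not shown.

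A reader might infer two stronger things. One is that the attended-sessions rule scores failures as successes on a large scale, because about 75% of EA and 50% of sham dropouts would qualify when they leave after 1–6 sessions. Those percentages arise only by giving dropouts the completers' relief rates, so they do not describe failures; with low relief rates few dropouts qualify. The other is that the rule is biased whenever dropout differs by arm. The 35%/15% example does not show this: relative to equal dropout, the attended-sessions difference moves from 33.0 to 30.5 points, while the all-sessions difference moves from 26.8 to 11.8. Choosing between the rules is partly a choice of estimand.

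**Conclusion.** The contradiction is in the text, concerns the primary endpoint, and must be resolved before unblinding. The rules are guaranteed to agree only for full attenders, and the article itself allows for 25% dropout, or 7 to 8 of 30 per arm.

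Under the stated assumptions the choice of rule moves power from 84–91% to 56–82%. The 56% is the unfavourable end, where every dropout leaves too early to reach seven yes answers. The gap shrinks as dropouts leave later and nearly vanishes if early leavers rarely report relief. Independence of visits is a convenience; repeated answers from one person are likely to be correlated. The direction and size of any bias depend on who leaves and when, which the document does not give. The sample size arithmetic is not in error.

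**What to change.** State one rule in both the Primary outcome and Statistical analysis sections. Applying the definition under Outcome measurement: a responder answers yes at 7 or more of the 12 scheduled AR assessments; assessments that are missed or fall after withdrawal count as not relieved; every randomised participant is in the denominator. This also settles the 0/0 case. Report the attended-sessions rule as a sensitivity analysis.

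Restate the power under Sample size calculation for this endpoint as a range with its assumptions, for example 56%, 68% and 82% for dropout after 1–6, 1–11 and 7–11 sessions.

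The change needs no new data or procedures, only wording and a restated power. It has two real costs. The stated power becomes less favourable. The all-sessions rule also counts dropout as failure, so it responds to unequal dropout by design; the text should say so, and the sensitivity analysis should be read alongside it.

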#### Randomization and allocation concealment

Sixty participants will be randomly assigned to either the EA or sham EA group. A random number table will be generated using block randomization with blocks of four by R for windows 3.2.1 (R Foundation for Statistical Computing, Vienna, Austria); to this end, the block randomization function will be used with blocks of four. The allocations will be kept sealed in a double-locked cabinet by an independent statistician. If the participants pass the screening test, they will be allocated according to the procedure above to conceal the allocation from both investigators and participants. After allocation, the statistician will email a unique random number and participant group allocation to both the clinical research coordinator and the Korean medicine doctors (KMDs). This feedback document will be kept in the master file for the trial.

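### Safety is analysed by ITT, so anyone randomised but never treated stays in the adverse-event denominator: a small effect of either sign between arms, removable with one sentence (minor)

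*Protocol article*

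**What the plan says.** The Statistical analysis section sets the general rule, "We will perform both intention-to-treat (ITT) and per protocol (PP) analysis, with all analyses being based on the ITT principle", and extends it to harms: "The analysis for safety will also follow the principles of ITT". The only set that depends on exposure is per protocol: "Any participant who receives EA more than nine times during the study period will be eligible for PP analysis".

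Allocation comes before treatment: "If the participants pass the screening test, they will be allocated according to the procedure above" (Randomization and allocation concealment). Twelve sessions are planned. One ground for withdrawal is to "miss a scheduled EA treatment three times in a row" (Withdrawal criteria).

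AEs are asked about at each visit (Safety; Table 2 marks V2 to V13). The chi-square or Fisher's exact test is to be used for nominal variables "as well as to compare AEs between groups" (Secondary outcomes, under Statistical analysis). The sample size section allows for dropout with one overall figure, "Assuming a 25 % of dropout rate", not split by arm or by whether it falls before or after the first session.

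**The concern.** ITT protects the randomised comparison of efficacy. For harms it has a side effect: a person who had no session cannot have an AE caused by a session, yet counts as one of those at risk. Someone randomised who misses the first three sessions would be withdrawn with no exposure and would still sit in the denominator. The per-protocol set is no substitute, since it drops the early leavers in whom intolerance would show.

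A second, separate matter is unequal exposure. A participant who leaves after a few sessions has had fewer chances of an AE and fewer enquiries about one, and a test on proportions treats that person like someone who completed 12 sessions.

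The abstract names safety, with efficacy, as a main purpose of the trial. With 30 per arm, a few people visibly move a percentage.

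**Working it through.** **Inputs from the article.** 30 per arm; 12 planned sessions; 25% dropout. The sample size figures reproduce: the pooled-variance formula for 92.8% against 57.1% gives 21.91 (the article has 21.9), and 21.9/0.75 = 29.2, rounded up to 30. They do not bear on the point beyond supplying the 30 and the 25%.

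**Assumptions.** The article does not define ITT further; I read it in the usual sense of all randomised participants, as allocated. It gives no AE rate and no number never treated, so both are assumed below. Never-treated participants are taken to have no recorded AE.

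**Step 1: denominator effect in one arm.** Let *a* participants have an AE and *u* be never treated. The ITT proportion is a/30 and the treated proportion is a/(30 − u). Their ratio is (30 − u)/30, so the relative understatement is u/30 whatever the AE rate.

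| u | u/30 | ITT proportion if the treated proportion is 30% |
|---|---|---|
| 0 | 0% | 30% |
| 1 | 3.3% | 29% |
| 2 | 6.7% | 28% |
| 3 | 10% | 27% |
| 8 | 26.7% | 22% |

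The last row is an outer bound: 25% of 30 is 7.5, taken as 8, with every dropout placed before the first session. As a count, 6 participants with an AE are 6/30 = 20.0% by ITT and 6/27 = 22.2% of the treated when three were never treated.

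**Step 2: difference between arms.** Assume treated proportions of 30% (EA) and 10% (sham), a difference of 20 points. The ITT difference is 30% × (30 − u_EA)/30 − 10% × (30 − u_sham)/30.

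- Two never treated, EA only: 28.0 − 10.0 = 18.0 points.
- Two, sham only: 30.0 − 9.3 = 20.7 points.
- Eight, EA only: 22.0 − 10.0 = 12.0 points.
- Eight, sham only: 30.0 − 7.3 = 22.7 points.

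The sign depends on the arm in which the untreated people fall.

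**Step 3: early leavers.** Assume an AE risk of 3% per session, unrelated to leaving. Over 12 sessions the proportion with any AE is 1 − 0.97^12 = 30.6%. If 25% leave after *m* sessions, it is 0.75 × 30.6% + 0.25 × (1 − 0.97^m): 25.1% for m = 3 and 27.1% for m = 6. With equal risk per session but 25% leaving EA and 5% leaving sham, all after 4 sessions (1 − 0.97^4 = 11.5%):

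- EA: 0.75 × 30.6% + 0.25 × 11.5% = 25.8%
- Sham: 0.95 × 30.6% + 0.05 × 11.5% = 29.7%

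Everyone here had at least one session, so an at-least-one-session set gives exactly the same proportions. The shortfall comes from exposure, not from ITT. A rate per session does remove it under these assumptions: expected sessions are 30 × (0.75 × 12 + 0.25 × 4) = 300 in EA and 30 × (0.95 × 12 + 0.05 × 4) = 348 in sham; expected AEs are 3% of each, 9.0 and 10.4; both rates are 3 per 100 sessions.

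**Step 4: if leaving is caused by harm.** Keep 3% per session for those who stay, and suppose that each of the 25% who leave had an AE. The ITT proportion is then 0.25 + 0.75 × 30.6% = 48%, above 30.6%. The direction found in Step 3 therefore holds only when leaving is unrelated to AEs.

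**The case against.** A reader might infer more: that ITT as such understates harm, and most in the arm with more dropout. The article does not support that. Dropout after the first session leaves the denominator at 30 under either set (Step 3). The 25% is a single planning allowance, with nothing to show that it differs by arm or precedes treatment. Never-treated participants in the sham arm would enlarge the EA-minus-sham difference (Step 2). Participants who leave because EA is poorly tolerated would usually have a recordable AE, which ITT keeps and counts (Step 4). Nor is it a fault to keep briefly treated participants: they were exposed, and excluding them could hide the AEs that made them leave.

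There is also a fair defence of the sentence itself. An all-randomised tabulation is transparent, and a reader can recompute a treated-only percentage if participant flow is reported. AE ascertainment is fuller than the test alone suggests: enquiry at every visit, recording of severity, duration and cause, causality assessed by the investigator, and review of causes by an independent monitor. No crossover between devices is described, so grouping by treatment received may move nobody. Rates and exact denominators are often left to a statistical analysis plan, which is not shown here.

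Most of this stands and keeps the point small. It does not remove it, because the article does not leave the safety set open: it fixes ITT, and offers per protocol as the only alternative.

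**Conclusion.** The point holds in a limited form and is minor. Safety by ITT lowers an arm's AE proportion only through participants randomised but never treated. The size is u/30: 3.3% relative for one, 6.7% for two, nil for none, and 26.7% only in the unlikely case that all expected dropout precedes treatment. This rests on reading ITT as all randomised participants and on their having no recorded AE; the actual count cannot be known from the article. The effect on the between-arm difference can have either sign.

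Unequal exposure among early leavers is a separate limitation of comparing proportions by chi-square or Fisher's exact test. A new analysis set does not touch it; an exposure-based rate does, to the extent that AE risk is roughly constant per session.

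**What to change.** Replace the safety sentence in the Statistical analysis section with: *Safety will be analysed in all participants who received at least one session, by treatment received, reporting by arm the number of sessions, the proportion with any AE, and the AE rate per 100 sessions with 95% CI.* An all-randomised tabulation may be kept as a supplement.

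The cost is one sentence. AEs are already collected at every visit, and sessions must be counted anyway to apply the per-protocol rule. The downside is that the safety denominator may differ slightly from the efficacy denominator, which the participant flow can explain. One participant may have several AEs, so the interval for the rate should allow for repeated events within a person.
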